#### Target Participation Rates

We aim for high participation rates in all interest groups. Specifically, at least 85% of health care professionals [30,31], and 85% of relatives should participate in the baseline survey (*t*_0_), and at least 80% of patients should participate in the follow-up survey (*t*_1_) [31-36]. These rates relate to the planned recruitment numbers (approximately 250 health care professionals and 125 patients and relatives). Participation will be measured at 2 time points: at the beginning of the study (t0) for health care professionals and relatives, and at a later time point (*t*_1_) for all groups. Participation is documented to compare the planned with the actual number of participants.

#### Definition of Participation Rate

For health care professionals and relatives, participation refers to their involvement in the first survey assessment (*t*_0_). Completion of the follow-up survey (*t*_1_) for health care professionals and relatives is evaluated separately as part of the dropout analysis. For patients, participation refers to the completion of the single planned survey (*t*_1_), as patients are surveyed only once and no longitudinal follow-up is foreseen.

#### Dropout Rate

We define dropout as incomplete participation between *t*_0_ and *t*_1_ among those who had originally agreed to participate. For health care professionals and relatives, dropout is assessed across the 2 survey time points; for patients, it refers to the ratio of respondents in the survey (*t*_1_) to the number of recruited patients who provided informed consent during their ICU stay. The dropout rate should not exceed 35% of those who originally consented [30,34,36].

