### Pilot Effectiveness Evaluation

#### Overview

Although the intervention and its evaluation are closely linked, they represent 2 methodologically distinct components of the project. The intervention involves the permanent integration of clinical study therapists into the intensive care team.

The accompanying study systematically evaluates the feasibility of conducting an RCT to evaluate the intervention. Key criteria for the feasibility of the RCT include participation and dropout rates, data completeness, and the overall practicability of the administered questionnaire. The feasibility of the intervention is assessed in terms of participation, dropout rates, fidelity, and acceptance. Both quantitative and qualitative methods are applied.

The study is aimed at 3 groups in intensive care: patients, their relatives, and health care professionals.

Planned sample sizes are (1) up to 125 patients and their relatives during the course of the study, and (2) approximately 250 health care professionals. The planned sample size is based on feasibility considerations rather than a formal statistical power calculation. In line with recommendations for pilot and feasibility trials, the sample is intended to provide sufficient information on recruitment processes, data completeness, and variability of candidate outcome measures to inform the design of a subsequent definitive trial.

The standardized survey is conducted with health care professionals at 2 measurement points: a baseline survey (*t*_0_), which is administered within 6 weeks of the start of the intervention for health care professionals and a second survey (*t*_1_) at the end of the intervention phase. Relatives and patients are recruited during the patient’s ICU stay; however, only for relatives, a baseline survey (*t*_0_) is administered during that time to avoid placing a high burden on patients. The follow-up survey (*t*_1_) is conducted with relatives and patients 4 months after discharge from the ICU.

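### Patient dropout is defined as the response rate, which reverses the 35% limit; once corrected, the limit is redundant beside the 80% participation target for up to 125 consents

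*Protocol article*

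**What the plan says.** The Dropout Rate section under Feasibility of an RCT starts with a general definition: "We define dropout as incomplete participation between" t0 and t1, among people who had agreed to take part. It then gives a formula for patients, who are surveyed only once: "for patients, it refers to the ratio of respondents in the survey" at t1 "to the number of recruited patients who provided informed consent during their ICU stay". It closes with the ceiling: "The dropout rate should not exceed 35% of those who originally consented".

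Patient participation rests on the same questionnaire. Definition of Participation Rate states: "For patients, participation refers to the completion of the single planned survey". Target Participation Rates asks that "at least 80% of patients should participate in the follow-up survey" and fixes the denominator: "These rates relate to the planned recruitment numbers (approximately 250 health care professionals and 125 patients and relatives". The Overview under Pilot Effectiveness Evaluation gives the planned sample as "up to 125 patients and their relatives during the course of the study".

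Feasibility Evaluation combines these in a traffic-light rule. The Proceed tier needs participation of 80% or more in every group, dropout of 35% or less and missing core data of 20% or less. Participation of 60% to 79% leads to the modification tier, and below 60% in key groups to the stop tier. Neither of the lower tiers gives a dropout value.

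**The concern.** Respondents divided by consenters rises as follow-up improves. A ceiling on that quantity penalises good follow-up and rewards poor follow-up: a 90% return would count as 90% dropout and fail. Dropout is one of the four core criteria for RCT feasibility and part of the Proceed tier, so a formula pointing the wrong way for one of three groups affects the progression decision. No other section of the article gives a correct patient formula.

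A second question remains after the formula is turned round. Patient participation and patient dropout both use the t1 return as their only outcome, but with different denominators. It is worth knowing whether the two thresholds fit together, and whether they let a reader separate failed recruitment from failed follow-up.

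**Working it through.** **Inputs.** R = patient questionnaires returned at t1. C = patients who consented in the ICU. Planned patients = 125 (Target Participation Rates; Overview). Dropout ceiling = 35% (Dropout Rate). Participation target = 80% (Target Participation Rates). The article derives no figure from these thresholds, so there is none to reproduce; the check converts them to counts.

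**Step 1: the formula as written, R/C ≤ 0.35.**
- With C = 125: R ≤ 0.35 × 125 = 43.75, so at most 43 returns pass.
- The participation target needs R ≥ 0.80 × 125 = 100.
- For any C up to 125, a literal pass means R ≤ 43, so both criteria cannot be met. At 43 returns, participation is 43/125 = 34.4%, in the stop tier.
- Illustration with the May 2025 counts in Results: 6/72 = 8.3% would pass as dropout, with 66 of 72 questionnaires not yet returned.

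**Step 2: the complement, 1 − R/C ≤ 0.35, so R ≥ 0.65 × C.** Participation is R/125.

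| Consents C | Fewest returns with dropout ≤ 35% | Dropout at that count | Participation at that count | Dropout implied by 100 returns |
|---|---|---|---|---|
| 72 | 47 | 34.7% | 37.6% | not attainable |
| 100 | 65 | 35.0% | 52.0% | 0% |
| 110 | 72 | 34.5% | 57.6% | 9.1% |
| 125 | 82 | 34.4% | 65.6% | 20.0% |

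- With C = 125, 100 or more returns satisfy both criteria. Returns of 82 to 99 satisfy the dropout limit and miss the 80% target.
- For any C ≤ 125, R ≥ 100 gives 1 − R/C ≤ 1 − 100/125 = 20%. The participation target therefore always implies the dropout limit.
- The dropout limit could be the deciding one only with more consents: 100/0.65 = 153.8, so from 154 consents upward.

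**Step 3: the denominators.**
- With 72 consents, 47 returns meet the dropout limit (34.7%) but give 37.6% participation.
- Even 72 returns from 72 consents, with no dropout at all, give 72/125 = 57.6%, below the 60% line.
- So the two measures can give opposite verdicts on the same returns when consents fall short of 125.

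**The case against.** The strongest reply is that the intent is plain. The sentences before and after the patient clause both describe loss among consenters, so the clause merely omits the complement. The article also treats its thresholds as pragmatic benchmarks, not rigid rules. The intent is indeed clear, which is why the repair is short. But this clause is the only operative formula for patients, and even a benchmark needs a direction.

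Several stronger readings are tempting, and the documents do not support them:

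- **That the 35% and 80% thresholds still contradict each other after the correction.** They do not: 100 or more returns of 125 meets both. One criterion being stricter than another is normal in a multi-part rule. The redundancy applies to patients only, because professionals and relatives have participation measured at t0 and dropout at t1.
- **That patient recruitment is not measured.** The participation denominator is planned recruitment, so too few consents lower the rate, and fewer than 100 make 80% unattainable. What patients lack is a separate threshold for the consent step.
- **That 6 of 72 shows failing follow-up.** It is an interim count. Patients are surveyed four months after consent and inpatient stay, so an unknown share of the 66 were not yet due. It shows only how the formula behaves.
- **That participation should become consented over approached.** The article says its core criteria are those in the study registration and that data collection ran through June 2025. Such a change would alter a registered criterion after collection, and it needs counts of patients approached, which the article does not show were kept.

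**Conclusion.** The patient dropout definition is wrong as written and should be corrected before the feasibility criteria are assessed. It states the response rate, contradicts the general definition in its own paragraph and reverses the ceiling: at most 43 of 125 returns would pass, against the 100 needed for participation.

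Once corrected, the 35% limit does not conflict with the 80% target but is redundant for the patient Proceed verdict, since the target already implies dropout of 20% or less. A loss at the limit leaves 82 returns (65.6%), in the modification tier. The different denominators mean that a low participation figure alone cannot show whether consent or follow-up fell short.

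This rests on two readings: that the figure of 125 means 125 patients, and that consents do not exceed it. The redundancy would persist up to 153 consents and end at 154. The error in the definition depends on neither reading.

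**What to change.** 1. Replace the patient clause in Dropout Rate with: patient dropout = 1 − (t1 respondents / patients who consented in the ICU). This is one sentence, recorded as a clarification before analysis. It needs no new data and brings the clause into line with the rest of its paragraph.
2. Add a note that, with consents at or below 125, the 80% participation target is stricter than the 35% limit for patients, so the limit does not decide the Proceed verdict in that group.
3. Report two patient ratios beside the registered criteria: consents/125 for recruitment and t1 returns/consents for follow-up. Their product is t1 returns/125, the participation rate, so a shortfall can be assigned to one step or the other. For example, 60 returns from 72 consents would be 57.6% × 83.3% = 48.0%, which points mainly to recruitment. Both ratios use counts the study already holds.

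Leave the registered definition of patient participation unchanged.

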#### Practicability of the Survey

Practicability is assessed using short evaluative items embedded in the t1 questionnaires for all groups. These items capture tolerability (perceived burden and length of the questionnaire), relevance (perceived meaningfulness and usefulness of the questions), and comprehensibility (clarity and understandability of the items).

These indicators allow us to judge whether the survey instruments are acceptable and feasible under routine ICU conditions, and whether adaptations are required for a subsequent definitive RCT.

#### Data Completeness

Another important criterion is the completeness of data collection. For each target group and survey time point, the proportion of missing data will be monitored and reported. Acceptable thresholds are 20% or less missing data for core outcome variables [38].

### Feasibility of the Intervention

The psychosocial intervention used as part of the study was developed to address challenges in intensive care identified in phase A. To evaluate the feasibility of implementing the intervention, we assessed the following 4 core criteria, in alignment with the OSF preregistration [39].

#### Participation Rate

The IPS intervention is conceptualized as a systemic intervention: its implementation is tied to the participating ICU ward rather than individual use. All patients, relatives, and health care professionals on the intervention wards are considered part of the intervention group, regardless of whether they actively use individual intervention components. Both direct participation (eg, use of specific tools) and indirect effects (eg, reduced burden through the psychologist’s presence) are relevant.

Therefore, individual-level participation rates cannot be meaningfully predefined or assessed. Instead, individual participation is evaluated descriptively based on the intervention’s reach and documented activities, such as the frequency and type of contacts recorded by the study therapists.

At the ward level, participation is defined as the successful implementation of the IPS model in the assigned ICU. All ICUs randomized to the intervention arm are expected to implement the intervention as planned, corresponding to a ward-level participation rate of 100%.

#### Dropout Rate

As the IPS intervention is systematically implemented at the ward level and does not include an obligatory number of components to be administered due to its needs-based approach, individual dropout is not defined in the conventional sense. While it is possible to document whether patients, relatives, or health care professionals discontinue contact with the study therapists, this information primarily serves to describe intervention reach rather than to calculate a formal dropout rate. Instead, contact frequency and reasons for noncontinuation are documented descriptively by the study therapists to inform internal evaluation and interpretation of implementation dynamics. Dropout was assessed at the ward level (ratio of intervention wards on which the intervention was implemented but then discontinued). No predefined threshold for dropout was established for the intervention.

#### Fidelity

Fidelity refers to the extent to which the intervention was implemented as intended. This includes adherence to the intervention manual, the documented presence of study therapists according to duty rosters, the correct implementation of intervention modules (eg, delirium prevention and grief counseling), and weekly self-assessments by study therapists regarding their team integration. All procedures are documented centrally and monitored for deviations. A fidelity rate of 80% or more across these components is targeted [31,36,37].

#### Acceptance

The acceptance of the intervention is assessed via participant evaluations collected through standardized questionnaires at the end of the intervention phase. Participants (patients, relatives, and health care professionals) are asked to assess the relevance, support quality, and helpfulness of the intervention. At least 70% of respondents should rate the intervention as “rater helpful” or “very helpful” [32,37].

In addition to the questionnaire-based evaluation at *t*_1_, acceptability among health care professionals was assessed using the Acceptability of Intervention Measure in a separate, anonymous paper-based format. The Acceptability of Intervention Measure was distributed during scheduled team meetings on the intervention wards, with questionnaires completed either on site or returned later by health care professionals who were not present at the meeting. This procedure ensured broad coverage of health care professionals’ perspectives while maintaining anonymity and methodological consistency with the preregistered process evaluation [40].

### Additional Implementation Indicators (For Internal Evaluation)

In addition to the 4 preregistered feasibility criteria, further indicators are used for internal process evaluation:

Training fidelity: participation of study therapists in initial training, supervision, and intervision.Manual adherence: use of basic and toolbox elements as documented; 80% or more correspondence with the manual [37].Personnel stability: documentation of staffing changes or early terminations in study therapist roles.Completeness of documentation: proportion of missing data in study therapist protocols (threshold ≤20%).Perceived barriers to implementation: structural or organizational obstacles recorded by study therapists.Additional support needs: documentation of ad hoc psychosocial support (eg, night or weekend).Structural classification: contextual ward data (eg, staffing ratio and occupancy).

### Process Evaluation and Methodological Triangulation

To complement the predefined feasibility criteria, we conducted a qualitative process evaluation during the intervention phase. In addition to qualitative interviews, the process evaluation included documentation data from the study therapist, informal field observations by the research team, and contextual notes. Starting from the fourth month after implementation began, guided interviews were conducted with all 4 study therapists and 2 to 3 health care professionals per participating ward. The aim was to explore the acceptance and implementation of the intervention, as well as the pilot-study, in routine clinical settings and to identify contextual influencing factors. This substudy does not constitute an independent feasibility assessment but serves to contextualize and deepen the interpretation of the quantitative results.

### Methodological Triangulation

To gain a comprehensive understanding of feasibility, acceptance, and implementation, we triangulate multiple data sources: standardized questionnaires, qualitative interviews, and continuous process documentation. The details of the data sources are as follows:

Standardized surveys provide quantitative data on psychosocial well-being, stress, and acceptance.Qualitative interviews capture subjective perspectives and contextual factors.Continuous process documentation reflects practical aspects, such as implementation challenges, the use of specific intervention modules, flexibility in application, and perceived implementation barriers.

Figure 1 illustrates the chronological alignment of data collection with participant groups and methodological components.

**Figure 1. F1:**
[figure not shown]
Components and timeline of the study in phase B. ICU: intensive care unit; IPS: Integrated Psychosocial Care; RCT: randomized controlled trial.

Additionally, documentation by STs systematically captures the use of toolbox elements and barriers to implementation. The process data are recorded continuously throughout the intervention phase and are used to support internal quality monitoring.

The triangulation of these sources supports a nuanced interpretation of findings, facilitates the identification of tensions or contradictions, and enhances contextual insight into structural and individual factors influencing feasibility. This integrated perspective provides a foundation for assessing prerequisites for a subsequent effectiveness study.

### Ethical Considerations

Before the start of the intervention, ethical approval for phase B was obtained from the ethics committees of the University of Ulm (112/24) and the University Medical Center Magdeburg. Charité—Universitätsmedizin Berlin accepted these approvals in accordance with §15 (2) of the professional code of the Berlin Medical Association. The study is conducted in accordance with the Declaration of Helsinki and the DFG’s (Deutsche Forschungsgemeinschaft) guidelines for safeguarding good scientific practice, and complies with the European Union General Data Protection Regulation (GDPR) and the Federal Data Protection Act. A comprehensive data protection concept was developed for phase B and approved by the data protection officers at all participating sites. It considers the specific requirements of data collection, storage, and analysis within a multicenter feasibility study. Given the noninvasive nature of the intervention, no serious intervention-related adverse events are expected. Nevertheless, potential psychological burden associated with study participation (eg, distress during questionnaire completion) will be monitored descriptively through participant feedback and process documentation. Any unintended effects will be documented and considered in the overall feasibility assessment.

All personal data collected during the study (eg, interview data) are subject to a 2-stage pseudonymization process. The first pseudonymization takes place locally at the point of data collection. The allocation keys are then managed by an independent trusted third party located at the University Medical Center Magdeburg, which is responsible for storing identifying data separately from study data, organizing follow-up contacts, and ensuring compliance with all data protection requirements.

Reidentification is only possible via the trusted third party. Pseudonymized data are stored centrally, and access to study-relevant data is restricted to authorized scientific staff. A password-protected, access-restricted project platform serves as the technical infrastructure. Upon completion of the study and the expiration of legally mandated retention periods, all data will be deleted in accordance with data protection requirements.

Participation in the study is voluntary and based on written informed consent. Participants are informed of their rights under Articles 13, 14, 15, 17, and 21 of the GDPR, including the right to access their personal data, the right to correct inaccurate data, the right to deletion after study completion, request deletion after study completion, and the right to withdraw consent at any time without providing reasons. No compensation is provided for participation.

### Registration

The study protocol for phase B is registered on the OSF Registries [41] and ClinicalTrials.gov (NCT06733493).

This protocol follows the SPIRIT (Standard Protocol Items: Recommendations for Interventional Trials) 2013 statement (Checklist 2) [42].

Publications in peer-reviewed, open-access journals, including *JMIR Research Protocols* [10], where the protocol for phase A of the IPS-Pilot project has already been published.Presentations at relevant national and international scientific conferences, particularly in the fields of intensive care medicine, psychosomatics, and implementation research.Summary reports and targeted dissemination materials for clinical stakeholders and health policy representatives, aimed at informing implementation strategies for integrated psychosocial interventions in intensive care settings.

## Results

The intervention was launched as planned in July 2024 and is being implemented over a period of 12 months in 8 general ICUs. Data collection is staggered and target group–specific as follows:

Health care professionals: the baseline survey (*t*_0_) was completed in the first 6 weeks of the intervention. A total of 177 participants completed the baseline questionnaire. The follow-up survey (*t*_1_) is scheduled for the end of the intervention period.Relatives: The baseline survey (*t*_0_) is completed during the patient’s ICU stay. A follow-up survey (*t*_1_) is conducted 4 months after *t*_0_ to capture delayed psychosocial burden and changes over time. Recruitment for *t*_0_ took place continuously over 8 months and has been completed. A total of 82 fully completed *t*_0_ questionnaires are available. Eleven *t*_1_ responses have been received to date.Patients: the survey is conducted once (*t*_1_), 4 months after consent and inpatient stay. In May 2025, 72 consents to participate have been obtained and 6 questionnaires have already been completed and returned.

Parallel to the quantitative data collection, the qualitative accompanying research was conducted during the fourth month of the intervention phase. All planned interviews—with the study therapists and a total of 22 health care professionals from the participating wards—were completed and are currently being analyzed. Discussions were also held with patients and relatives on their perception of the study recruitment. In addition, data were collected on which toolbox measures were actually used and which barriers prevented their use. The weekly study therapist documentation on intervention implementation is ongoing. These process indicators demonstrate that recruitment and intervention delivery are feasible within the planned timeline and will provide the empirical basis for assessing the predefined feasibility criteria.

Data collection took place through June 2025. The initial study results are scheduled to be published in 2026, following the completion of data analysis.

